#### Survey 1 following child’s illness episode

Parents will receive an electronic survey when their child was called in ill or is sent home from childcare because of illness when parents provide consent to receive this additional survey during the 12-week study period. Parents will receive this survey within 14 days after each time their child becomes ill, followed by a total of two reminders which are sent out every 3 days.

#### Survey 2 and 3 on knowledge, attitude, self-efficacy, and risk perception

Knowledge, attitude, self-efficacy and risk perception towards fever will be measured by means of 7-point likert scales in a survey that is distributed electronically and on paper. Childcare staff in intervention and control group will receive this survey at baseline (T0) and after the 12-week study period (T6) to measure the change in behavioural determinants between and within intervention and control group. Parents will receive the survey at T6 to measure the difference in behavioural determinants between intervention and control group.

### Analysis

Statistical analysis will be performed with SPSS version 21.0 and a two-sided *p*-value smaller than or equal to 0.05 will be considered statistically significant. Due to repeated measures (every 2 weeks for 12-weeks study period) and possible missing data, the primary outcome measure will be analysed using linear mixed models, where the covariance structure of the repeated measures will be chosen based on the lowest Bayes information criterion (BIC). Illness absenteeism will be computed every 2 weeks of registration for each location to take into account fixed closing days of the childcare center during public holidays. Missing outcome data will not be imputed, since a likelihood based approach will be used with linear mixed models. No missingness in the explanatory variables such as group (intervention or control), time (0, 2, …, 12 weeks), group*time, and stratification variable cluster size (large or small) is expected.

Secondary outcome measures will be analysed on different levels and in different ways. The survey on knowledge, attitude and practices for childcare staff will be analysed on three levels. Time is the lowest level (level 1), which is nested within staff members (level 2), which are again nested within location (level 3). Linear mixed models will be used for numerical outcomes and logistic mixed models or generalized estimating equations (GEE) for categorical outcomes, where an unstructured covariance structure will be used in case of 2 or three repeated measures, otherwise the covariance structure of the repeated measures will be chosen based on the lowest BIC. In addition, a random intercept on location level will be included to account for the nesting of staff members within a location. The same survey will be analysed for parents on two levels with parents as lowest level (level 1), which is nested in location (level 2), because only a post-allocation measurement will be performed to compare parents in intervention group with those in control group. In this case, a random intercept on location level is included in the model to account for the nesting of parents within a location. Survey outcomes are measured on 7-point likert scales and the average outcome (sd) will be calculated per item after assessing scale quality. The parent survey following child’s illness absenteeism will be analysed by using descriptive statistics. All data will be obtained, managed and monitored according to the guidelines of Good Clinical Practice.

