### Sample size

Our primary outcome is absenteeism due to illness, defined as the percentage of childcare days absent due to illness on the total of childcare days during a 12-week period. We performed a pilot study among parents with children attending 21 childcare centres of MIK in Spring 2016 to calculate illness absenteeism. For this pilot study, an average 4-week illness absenteeism of 9.9% (sd = 18.035) was reported [unpublished observations], which was in agreement with the absenteeism rate reported by Hedin et al. in Swedish children [63]. To calculate our sample size we assumed an illness absenteeism of 9.9% in the control group. This cluster RCT aims to achieve a clinically significant reduction of illness absenteeism due to fever and common infections by 4.5% in the intervention group [4, 30, 64]. To obtain this difference with 80% power, assuming a within group SD of 18.035 and a significance level α of 0.05, 253 participants per group (506 in total) are required (PS Power and Sample size program, independent-samples t-test). Due to cluster (childcare location) randomisation, where we assume a mean number of 55 children per cluster and an intra-cluster coefficient of 0.01 into account, based on our pilot and previous literature [65], this number increases to 390 participants per group. After correction for 10% loss to follow-up and 10% efficiency loss based on unequal cluster sizes [66], the required sample size is 482 participants per group (total *n* = 964). To meet this sample size, this study aims to recruit 18 clusters (childcare location) with 55 participating children per cluster, resulting in 990 children.

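### The primary mixed model leaves within-location correlation to a BIC choice over 18 locations, without ruling out independence

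*Protocol article*

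**What the plan says.** The Allocation section randomises 18 childcare centres, nine to each arm. For the primary outcome, the Analysis section gives a linear mixed model with group, time, group by time and the centre-size stratum as explanatory variables. Dependence is handled by one rule: "where the covariance structure of the repeated measures will be chosen based on the lowest Bayes information criterion (BIC". No candidate structures are listed and no random effect is named.

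The same section says "Illness absenteeism will be computed every 2 weeks of registration for each location", which points to location-by-period data. The Outcomes section, however, defines the outcome as a child's own share of childcare days lost to illness over 12 weeks, and the Sample size section counts children, with 55 per location and an intra-cluster coefficient of 0.01.

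For the staff survey the article adds a location term explicitly: "a random intercept on location level will be included to account for the nesting of staff members within a location". The parent survey model also gets a location random intercept. Significance is judged by "a two-sided *p*-value smaller than or equal to 0.05 will be considered statistically significant".

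**The concern.** Location is the unit of randomisation, so the primary test is valid only if the model allows for correlation within location. Here that correlation is not fixed in advance but is whatever BIC prefers. BIC charges for each extra covariance parameter. With 18 locations it can favour independence even though a persistent location effect exists.

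On location-level data with six 2-week periods, independence turns 18 x 6 = 108 location-periods into separate observations. With 13 fixed-effect parameters (intercept 1, group 1, time 5, group by time 5, stratum 1) that leaves 95 residual degrees of freedom. A between-location comparison has 18 - 3 = 15. The standard error of the group effect is then too small as well.

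The unclear unit adds a second route to the same problem: if children were modelled, as the outcome definition and sample size suggest, no location term is stated.

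**Working it through.** **1. The plan's sample size, reproduced.** The inputs are in the Sample size section: "we assumed an illness absenteeism of 9.9% in the control group", a "reduction of illness absenteeism due to fever and common infections by 4.5% in the intervention group", and "To obtain this difference with 80% power, assuming a within group SD of 18.035 and a significance level α of 0.05, 253 participants per group".

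- Unclustered: n = 2 x (1.9600 + 0.8416)^2 x 18.035^2 / 4.5^2, about 252.1, so 253 per group. The 4.5% is therefore an absolute difference.
- Design effect: 1 + (55 - 1) x 0.01 = 1.54. 253 x 1.54 = 389.6, so 390.
- Two 10% allowances: 390 / 0.9 / 0.9 = 481.5, so 482.

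The sizing is consistent and does count clustering.

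**2. Correlation between periods implied by these inputs.** Total variance is 18.035^2 = 325.3.

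- Between locations: 0.01 x 325.3 = 3.25.
- Within, for a mean of 55 children: 0.99 x 325.3 / 55 = 5.85.
- Correlation of two period means of one location: 3.25 / (3.25 + 5.85) = 0.36.

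This assumes that the pilot's 4-week SD holds for 2-week periods. If the within-location variance doubled in the shorter window, the value would be 3.25 / (3.25 + 11.7) = 0.22. Children who are persistently prone to illness would push it up. The true value is unknown.

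**3. What independence does.** With compound-symmetric correlation r, the variance of a location's six-period mean is (1 + 5r) times what independence assumes: 1.5 at r = 0.1, 2.0 at r = 0.2 and 2.8 at r = 0.36. The harm also depends on how often BIC selects independence.

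**4. Null simulation.** Settings: 18 locations (9:9), six periods, complete and balanced data, REML, lowest BIC among independence, compound symmetry (CS) and AR(1), test of the time-averaged group effect at 0.05. When AR(1) was chosen, 35 df were assumed. The 6,000-replicate runs omitted the stratum.

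| Correlation | Replicates | BIC chose independence | Type I error, BIC rule | Type I error, CS always fitted |
|---|---|---|---|---|
| 0.05 | 3,000 | 89% | 7.1% | 4.5% |
| 0.10 | 6,000 | 74% | 8.9% | 5.0% |
| 0.20 | 6,000 | 36% | 8.0% | 4.7% |
| 0.22 | 3,000 | 31% | 8.4% | 4.9% |
| 0.36 | 6,000 | 5% | 5.5% | 4.9% |
| 0.60 | 6,000 | under 1% | 5.0% | 4.9% |

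Further runs gave 6.9-8.0% at 0.05, 7.9-10.0% at 0.10 (the 10.0% from only 1,200 replicates), 7.9-9.2% at 0.20 and 5.2-6.7% at 0.35-0.36. A run with seven candidate structures and Satterthwaite df (600 replicates) gave 8.0% at 0.10 and 5.0% at 0.36, so the low-correlation inflation does not hang on the assumed 35 df.

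**5. Independence barred.** With BIC choosing only between CS and AR(1) (1,500 replicates, Monte Carlo SE about 0.6 points), type I error was 5.3%, 5.6%, 4.9% and 4.4% at 0.05, 0.10, 0.20 and 0.36.

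**6. Child-level data with no location term.** 2 x (1 - Phi(1.96 / sqrt(1.54))) = 0.114. At an ICC of 0.005 it would be 0.082, and at 0.02 it would be 0.174.

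**The case against.** The strongest reply is that absenteeism is computed for each location, so location is the subject of the repeated measures and no level lies above it. The repeated-measures covariance is then the right place for the clustering, and CS does the work of a random intercept. This stands. A reader might infer from the contrast with the survey models that the missing random intercept is itself the error, but the documents do not support that: staff and parents are individuals below location, so those models need a location term that location-level data do not.

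Second, BIC selection as such is not the cause. With independence barred, the error stays near 5%. The article lists no candidates, and a list may exist in a fuller document. This also stands, and it makes the inflation conditional. It does not remove the point: the rule printed for the primary outcome leaves independence open, whereas the article fixes the location term for the two surveys.

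Third, the correlation implied by the plan gives only about 5-7%, and the group-by-time test stayed at 4.3-6.2% in the runs that checked it. Both are correct. But the 0.36 rests on carrying a 4-week SD over to 2-week periods, and a primary test should not depend on that.

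A reader might also say that every secondary model has a location intercept. That is too broad: the illness-episode survey is only described, and no model is stated for incidence.

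**Conclusion.** The point holds in a conditional form. If independence is among the BIC candidates, the type I error of the time-averaged group effect is about 7-9% at between-period correlations of 0.05-0.2, and about 5-7% near 0.36. At 0.6 there is no inflation, nor is there any if independence is excluded. These figures assume 18 equal-sized locations with complete data.

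It would be wrong to say that the plan as written inflates the type I error outright, or that its error is 11%. The 11% applies only if children are modelled with no location term, and the Analysis section points to location-level computation instead. That figure matters because the child-level definition and sizing leave the unit of analysis open to that reading.

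**What to change.** Amend the Analysis section in three respects:

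- State the unit of the primary analysis, location by 2-week period or child by period, and reconcile it with the child-level definition in the Outcomes section.
- Always keep a within-location correlation term: a location random intercept or, for location-level data, CS by location. Use Satterthwaite or other small-sample degrees of freedom.
- Let BIC choose only among structures that retain this term. Do not add CS on top of a random intercept, because the two cannot be estimated separately.

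This takes about two sentences and no new data. The price is slightly wider confidence intervals if the true location variance is near zero.

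### Staff survey: fitted with separate arm means at T0, the repeated-measures model reduces to a change-score comparison; sharing one T0 mean would give a modest, free gain in precision

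*Protocol article*

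**What the plan says.** Protocol article, section on Surveys 2 and 3: "Childcare staff in intervention and control group will receive this survey at baseline (T0) and after the 12-week study period (T6"), with the aim "to measure the change in behavioural determinants between and within intervention and control group". Table 1 places the first staff survey in the Enrolment column, ahead of the Allocation column.

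Analysis section, staff survey: "Time is the lowest level (level 1), which is nested within staff members (level 2"), with staff nested in location as level 3. For the covariance, "an unstructured covariance structure will be used in case of 2 or three repeated measures"; for the clustering, "a random intercept on location level will be included to account for the nesting of staff members within a location". The parent survey has only two levels because parents are measured once, which confirms that the extra staff level carries the T0 and T6 scores as two outcome records.

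No fixed effects are listed for the staff model. Those listed for the primary outcome are "group (intervention or control), time (0, 2, …, 12 weeks), group*time, and stratification variable cluster size (large or small"). The article nowhere mentions the T0 score as a covariate or a common T0 mean for the two arms.

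**The concern.** When a pre-randomisation score is an outcome and each arm has its own mean at that time, the model estimates an arm difference at T0 that randomisation makes zero in expectation. With two time points and complete pairs, group*time then becomes the difference in change scores: T0 is subtracted with weight 1, whatever its correlation with T6. A weight matched to that correlation has smaller variance.

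Knowledge, attitude, self-efficacy and risk perception are the four determinants that the intervention was built to shift, and they come first among the secondary outcomes. The article gives no sample size or power for the staff survey, so precision there is whatever the number of staff allows. The T0 data are already being collected, and the question is whether the model uses them well.

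**Working it through.** **Stated figures.** None exists for the staff survey. The sample size in the article is for children's absenteeism: "assuming a within group SD of 18.035 and a significance level α of 0.05, 253 participants per group (506 in total) are required". It reproduces: 253 × (1 + 54 × 0.01) = 389.6, rounded to 390; 390 / 0.9 / 0.9 = 481.5, rounded to 482. This point does not touch it.

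**Inputs from the article.** 18 locations, nine per arm; two time points; unstructured 2×2 covariance within staff; one random intercept per location, hence a location effect that is the same at T0 and T6.

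**Assumptions (not in the article).** m = 10 staff per location, all with both surveys; total variance 1 at each time; location ICC of 0.05, 0.10 or 0.20; T0–T6 correlation ρ of 0.3, 0.5 or 0.7 between a staff member's scores within a location; fixed effects group, time and group*time.

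**Step 1: location means.** Variance at each time v = (1 − ICC)/m + ICC. Covariance between times c = ρ(1 − ICC)/m + ICC. Correlation of location means k = c/v.

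**Step 2: the two estimators.** Apart from the common factor 2/9 for nine locations per arm:
- Separate T0 means (difference in change): 2(v − c).
- One shared T0 mean: v − c²/v = v(1 − k²).
- Ratio, shared to change: (1 − k²) / [2(1 − k)] = (1 + k)/2, below 1 whenever k is below 1.

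**Step 3: example.** ICC 0.05, ρ 0.3: v = 0.095 + 0.05 = 0.145; c = 0.0285 + 0.05 = 0.0785; k = 0.541; ratio 0.771.

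**Step 4: results.** Variance with a shared T0 mean relative to the change-score variance:

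| ICC | ρ = 0.3 | ρ = 0.5 | ρ = 0.7 |
|---|---|---|---|
| 0.05 | 0.77 | 0.84 | 0.90 |
| 0.10 | 0.83 | 0.88 | 0.93 |
| 0.20 | 0.90 | 0.93 | 0.96 |

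The exact generalised least squares variances of the three-level model, with and without the group main effect, give the same ratios. With the group main effect, the variance of group*time equals the change-score variance exactly in every cell. Taking the inverse square root, the change contrast's standard error is larger by 14%, 9% and 5% at ICC 0.05; 9%, 6% and 4% at 0.10; and 5%, 4% and 2% at 0.20.

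If ρ is instead read as the total correlation, including the shared location effect, the covariance is c = (ρ − ICC)/m + ICC. The ranges then become 0.76–0.90, 0.82–0.92 and 0.88–0.95.

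**Step 5: plain ANCOVA as an alternative.** Regress T6 on the individual T0 score with a location random intercept. If the slope is the within-location one (ρ), the variance is v(1 + ρ²) − 2ρc. Relative to the change contrast, for ρ = 0.3, 0.5, 0.7:
- ICC 0.05: 0.83, 0.88, 0.93
- ICC 0.10: 1.04, 1.03, 1.02
- ICC 0.20: 1.53, 1.38, 1.23

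A simulation with slope and variance components estimated by REML (1,500 runs per cell) gave 0.86, 0.88, 0.92; then 1.02, 1.02, 1.02; then 1.39, 1.24, 1.13. The gain has gone by an ICC of about 0.10 and is a loss at 0.20. The change contrast cancels a stable location effect, whereas an individual-level slope removes only part of it.

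**The case against.** The strongest reply is that the inefficient term is inferred. The staff paragraph gives levels, covariance and a location intercept but no fixed effects, and its wording would stand unchanged if the group main effect were omitted. A condensed article may leave that to a fuller document. This stands as a limit: the point is conditional on the fixed effects. The inference is still the natural one, because the stated aim is change between groups and the only fixed effects listed in the article include group and group*time.

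A second reply is that both estimators are valid and the choice is one of preference. The first half is right. But on these assumptions one has smaller variance at every setting tried, from data already in hand.

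Three stronger readings are tempting and the article does not support them:

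- *With only 18 locations, chance imbalance at T0 passes in full into the result.* Under the single location intercept specified, persistent differences between locations cancel in the change contrast. Only staff-level noise passes through.
- *Any baseline adjustment will do, with variance ratio (1 + ρ)/2.* That ratio ignores clustering. Step 5 shows that plain ANCOVA can do worse than the change contrast.
- *Within-group change is being offered as the intervention effect.* The article mentions it beside the between-group comparison and never calls it the effect, so it reveals no error.

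**Conclusion.** The point holds as a modest improvement in precision on a secondary outcome. If arm means are left free at T0, the staff analysis is a change-score comparison. A shared T0 mean would reduce its variance by 10–23% at an ICC of 0.05, 7–17% at 0.10 and 4–10% at 0.20, for ρ between 0.3 and 0.7. The benefit shrinks as ρ or the ICC rises.

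This rests on the assumed fixed effects, ρ, ICC and staff numbers, none of which the article gives for the staff survey. The exact equality with change scores applies to numerical outcomes and complete pairs; with missing surveys, or with the logistic or GEE analyses, it is approximate. A reader might infer that the planned analysis is biased or invalid. It is neither, and the primary outcome and its sample size are unaffected.

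**What to change.** State the staff model's fixed effects. Keep the three levels, the unstructured covariance and the location random intercept, and include the centre-size stratum. Fit time and group*time without a group main effect, so that both arms share one T0 mean. Report the group*time term, which is then the arm difference at T6, with its 95% CI. The constraint is justified because Table 1 puts the first staff survey before allocation. Staff with only one survey remain in the model. Do not offer ANCOVA on the individual T0 score as interchangeable with this.

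The cost is one sentence of analysis text. No new data are needed.

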As such, it is hypothesised that educating childcare staff on fever and infectious diseases may optimise decision making processes on illness absenteeism due to fever and common childhood infections, resulting in reduced childcare absenteeism, work absenteeism and use of healthcare services. To achieve this, it is important to obtain insight in which behavioural determinants influence decision making on illness absenteeism in childcare, and to target these determinants in the intervention. As childcare staff are also an important source of information for parents [33], it is expected that improved behavioural determinants of decision making among childcare staff will result in improved parental decision making on illness absenteeism.

This paper describes the development of a multicomponent intervention aiming to optimise decision making among childcare staff on illness absenteeism due to fever and common infections in 0-4 year-old attending childcare, and describes the study protocol of the cluster randomised trial evaluating the developed multicomponent intervention in childcare.

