### Outcomes

The primary outcome is absenteeism due to illness, defined as the percentage of days that the child is absent from childcare due to illness from the total number of childcare days during a 12-week period. This primary outcome will be used to evaluate the potential behavioural change in decision making on illness absenteeism, resulting from the multicomponent intervention that was developed to target behavioural determinants such as knowledge, attitude, self-efficacy and risk perception.

Secondary outcome measures are: 1) knowledge, attitude, self-efficacy and risk perception towards fever and common infections are measured among childcare staff and parents; 2) incidence rate of fever and common childhood infections; 3) number and duration of illness episodes in children who are called in ill or sent home because of illness during the study period, and whose parents complete a survey on this illness episode; 4) work absenteeism among parents who complete a survey when their child is called in ill or sent home because of illness during the study period; 5) healthcare service use for fever and/or common infections in children who are called in ill or sent home because of illness during the study period and of which parents complete an additional survey on this illness episode, 6) paracetamol use for fever and/or common infections in children who are called in ill or sent home because of illness during the study period and whose parents complete an additional survey on this illness episode.

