Secondary outcomes will be measured using two different surveys on different time points and for a different target group (Table 1). Survey 1 measures number and duration of illness episodes (3), work absenteeism (4), healthcare service (5), and paracetamol. Survey 1 is only sent to parents of which the child was ill during the study period and provided informed consent. The content of this survey is in line with surveys used in previous studies [19, 34, 42, 57, 58]. Survey 2 measures knowledge, attitude, self-efficacy and risk perception among childcare staff, whereas survey 3 measures these behavioural determinants among parents. Three vignettes were included to evaluate the decision making process of childcare staff and/or parents in three different cases of ill children based on the traffic light system that was implemented in the decision tool. These surveys on knowledge, attitude, self-efficacy, and risk perception for childcare staff and parents are developed based on previous research [19, 34, 58–61]. Survey items were operationalised according theories’ definitions of behavioural determinants. Subsequently, survey items were piloted among childcare staff to check understandibility and interpretation of items [62].

**Table 1 Tab1:** Time schedule of enrolment, intervention allocation, outcome assessments

			Study period						
	Enrolment	Allocation	Post-allocation						Close-out
Timepoint	*0*	0	*T* _*1*_	*T* _*2*_	*T* _*3*_	*T* _*4*_	*T* _*5*_	*T* _*6*_	
Enrolment:	X								
Eligibility screen	X								
Informed consent Survey 1 following child’s illness episode	X	X	X	X	X	X	X	X	
Informed consent Survey 2 knowledge, attitude, self-efficacy, risk perception childcare staff	X								
Informed consent Survey 3 knowledge, attitude, self-efficacy, risk perception parents									X
Allocation		X							
Interventions:									
Educational session Childcare staff		X							
Use of decision tool + booklet Childcare staff and parents		X	X	X	X	X	X	X	
Online video Childcare staff and parents					X				
Assessments:									
Children’s illness registration		X	X	X	X	X	X	X	
Survey 1 following child’s illness episode		X	X	X	X	X	X	X	
Survey 2 Knowledge, attitude, self-efficacy, risk perception Childcare staff	X								X
Survey 3 Knowledge, attitude, self-efficacy, risk perception parents									X

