### Allocation

Stratified block randomisation is conducted at the level of childcare centres, with nine centres randomised to our multicomponent intervention and nine centres randomised to care-as-usual (control). Intervention centres will receive all four components of the multicomponent intervention, control centres will provide care as usual. Stratification is based on size of childcare centres regarding number of children attending a childcare center. A small childcare center is defined as having fewer than 65 children attending childcare, while a large childcare center is defined as having more than 65 children attending childcare. The randomisation procedure is conducted by an independent researcher via http://www.randomization.com/. Childcare staff and parents will not be blinded after intervention allocation due to the nature of the multicomponent intervention. However, they are blinded to the primary outcome measure. Researchers will be blinded during data analysis to the allocation status of childcare centres.

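### Secondary outcomes 3 to 6 rest on Survey 1, for which only descriptive statistics are planned: no effect estimate, interval or allowance for clustering, although reductions in work absence and healthcare use are hypothesised

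*Protocol article*

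**What the plan says.** The Outcomes section of the protocol article numbers six secondary outcomes. It then assigns them to instruments: "Survey 1 measures number and duration of illness episodes (3), work absenteeism (4), healthcare service (5), and paracetamol". Paracetamol carries no number in that sentence but is outcome 6 in the list, so Survey 1 supplies four of the six.

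The Analysis section gives Survey 1 one sentence: it "will be analysed by using descriptive statistics". The other surveys are treated differently. The staff survey gets mixed models or GEE with a random intercept for location. For the parent survey on behavioural determinants, "a random intercept on location level is included in the model to account for the nesting of parents within a location".

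On expected effects, the Background hypothesises better decisions by staff, "resulting in reduced childcare absenteeism, work absenteeism and use of healthcare services". The Discussion again anticipates reductions in parental work absence and healthcare use.

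On entry to the survey, "Survey 1 is only sent to parents of which the child was ill during the study period and provided informed consent". The trigger is that the child is called in ill or sent home. Table 1 marks consent for Survey 1 at enrolment, at allocation and at T1 to T6. The Allocation section states: "Childcare staff and parents will not be blinded after intervention allocation".

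**The concern.** The trial names work absence and healthcare use among the things it expects to improve and lists them as secondary outcomes, but plans no estimate of the difference between arms. If the plan is followed as written, the report will hold percentages and means, perhaps by arm, with no planned measure of precision. Readers will compare them anyway, without allowance for the 18 locations or for several episodes in one child.

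A second difficulty limits what any analysis of Survey 1 can show. A record exists only after a child has been called in ill or sent home, which is the decision that the intervention is meant to change. Consent may also be given after parents know their arm. The surveyed sets can therefore differ between arms for reasons other than the effect on the outcome itself.

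**Working it through.** **The plan's own figure.** No sample size or precision is stated for any Survey 1 outcome. The Sample size section concerns the primary outcome only, and it reproduces:
- 253 per group for a difference of 4.5, SD 18.035, two-sided α 0.05 and 80% power (t-test power at 253 is 0.7998).
- Design effect 1 + (55 − 1) × 0.01 = 1.54; 253 × 1.54 = 389.6, rounded up to 390.
- 390 ÷ 0.9 ÷ 0.9 = 481.5, rounded up to 482.

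It neither supports nor contradicts this point.

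**Outcome against analysis.**
- Outcome 1, staff and parent determinants: Surveys 2 and 3, location-level models.
- Outcome 2, incidence rate: not assigned to Survey 1.
- Outcomes 3, 4, 5 and 6: Survey 1, descriptive statistics.

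The sentence on mixed models and GEE stands within the description of the staff survey. No other text plans an arm contrast for Survey 1.

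**How much clustering could matter.** Inputs from the protocol: 990 children, 18 locations, 12 weeks, 6.6 to 11.4 episodes per child-year (Background). Assumption: 25% of episodes yield a completed survey.
- 990 × 6.6 × 12/52 = 1,508 episodes; × 0.25 = 377 records; ÷ 18 = 21 per location.
- 990 × 11.4 × 12/52 = 2,604 episodes; × 0.25 = 651 records; ÷ 18 = 36 per location.

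Design effect DE = 1 + (m − 1) × ICC; the factor on the standard error is √DE.
- ICC 0.01 (the only ICC in the protocol, given for the primary outcome): DE = 1.20 to 1.35, factor 1.10 to 1.16.
- ICC 0.05 (assumed): DE = 2.00 to 2.75, factor 1.41 to 1.66.

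For a naive two-sided 5% test the true error is 2 × [1 − Φ(1.96/√DE)]. With an assumed 10 to 30 records per location it is 6.0% to 8.4% at ICC 0.01 and 10.4% to 21.1% at ICC 0.05. Repeated episodes in one child are not counted here.

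**Why a model alone is not enough.** An illustration on assumed numbers: 60 mild and 40 severe surveyed episodes, with consultation rates of 10% and 50%.
- Without the intervention: (60 × 0.10 + 40 × 0.50) ÷ 100 = 26%.
- If 45% of mild cases stay in childcare, 33 mild remain: (33 × 0.10 + 40 × 0.50) ÷ 73 = 32%.

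The rate among surveyed episodes rises although nothing changed within either severity group. A cluster-adjusted model of these records would reproduce that shift.

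**The case against.** The best defence is that description is the cautious choice. The survey is triggered by the behaviour under study, so declining to test on such a sample is defensible, and descriptive reporting of a secondary outcome is not an error in itself. The article says that secondary outcomes are handled in different ways, so the split looks deliberate. Survey 3 goes to parents generally, so its model is not a full precedent. The expected reductions are worded as possibilities, and power is set for the primary outcome alone. All of this stands, and it is why the estimates should carry an exploratory label. It does not justify having no estimate: an unadjusted table has the same selection problem and shows no uncertainty.

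Four stronger readings are tempting and are not supported:
- *That the trial can make no comparison on these outcomes.* The Analysis section does not exclude summaries by arm, and the illness register described under Primary outcome measure records symptoms and days absent in both groups. Absence episodes and days can be compared from it; duration of illness remains with Survey 1.
- *That standard errors will be understated by 1.4 to 1.7.* No standard error is planned for Survey 1, and that range needs an assumed ICC of 0.05. The 25% return is also assumed, and the episode rate counts all illness, not only illness leading to absence.
- *That late consent differs by arm.* Table 1 leaves it possible; nothing says how many parents consent late or whether arms differ.
- *That scoring every child without a registered absence as zero, and a child with an absence but no survey as missing, solves the problem.* Missingness would then depend on being absent, and an ill child kept in childcare who saw a GP or took paracetamol would count as a non-user. Both follow from what the intervention targets, and the result is likely to favour it.

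**Conclusion.** The point holds in this form: for four of six secondary outcomes the protocol fixes a descriptive analysis, and so plans no effect estimate, interval or clustering term. Two of the four, work absence and healthcare use, are named in the trial's own hypothesis. This is a stated method that does not serve the stated aim, not a detail left to an unseen analysis plan. It is worth correcting, but it does not touch the primary outcome or the sample size.

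The count of four rests on the text alone. The size of the clustering effect is not known from the documents: it ranges from slight (factor about 1.1 to 1.2) to material (1.4 to 1.7) on the assumptions shown. Even with clustering handled, the estimates describe surveyed illness absences and should not be read as effects on all children.

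**What to change.** Replace the sentence on Survey 1 so that it provides for the following:
- Compare outcomes 3 to 6 between arms with mixed models or GEE suited to the type of outcome. Include group, the centre-size stratum and a random intercept for location (with GEE, location as the cluster), and allow for child where episodes repeat. Report each difference with a 95% CI.
- Label these as exploratory estimates among surveyed illness absences. State the reason: entry depends on being called in or sent home ill, and on consent that remains open after allocation.
- Add a sensitivity analysis in parents who consented before allocation.
- For illness-absence episodes and days, add a comparison from the daily register over all registered children, using the same location-level model.
- Do not use the zero-if-no-absence, missing-if-no-survey analysis as the main one. If shown at all, show it as a sensitivity analysis with its likely bias toward the intervention stated.

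The cost is a few sentences of text and some extra analysis of data already planned for collection. The downside is small: intervals will be wide, the set that consented before allocation will be smaller, and the results can be claimed only as exploratory.
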